### Sensitivity analysis

A sensitivity analysis will be performed excluding multiple pregnancies and pregnancies complicated by preterm premature rupture of membranes.

To assess whether a subgroup effect is present, we will add an interaction term between the subgrouping variables and the treatment allocation to the regression model. When an interaction term is statistically significant (p<0.05), we will estimate the treatment effect within strata of the subgrouping variable.

Details of the statistical analysis will be describes in separate statistical analysis plan that will be completed before data lock.

### Cost-effectiveness analysis

The cost-effectiveness analysis will be done according to the intention-to-treat principle. Missing cost and effect data will be imputed using multiple imputation according to the Multivariate Imputation by Chained Equations (MICE) algorithm developed by Buuren.^31^ Rubin’s rules will be used to pool the results from the different multiply imputed datasets. Bivariate regression analyses will be used to estimate cost and effect differences between atosiban and placebo while adjusting for confounders if necessary. Incremental cost-effectiveness ratios (ICERs) will be calculated by dividing the difference in the mean total costs between the treatment groups by the difference in mean effect between the treatment groups. Bias-corrected and accelerated bootstrapping with 5000 replications will be used to estimate statistical uncertainty. Uncertainty surrounding ICERs will be graphically presented on cost-effectiveness planes. Cost-effectiveness acceptability curves will be estimated showing the probability that atosiban is cost-effective in comparison with placebo for a range of different ceiling ratios thereby showing decision uncertainty. Sensitivity analyses will be performed to assess the robustness of the results using different assumptions regarding costs and effects.

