### Procedures, recruitment, randomisation and collection of data

Potential participants will be identified by the local research co-ordinators and/or the staff of participating hospitals. Women eligible for the trial will be counselled by doctors, midwifes or research nurses trained in ‘good clinical practice’, and will be given a patient information form to read. Those who wish to participate, will be asked to give for written informed consent and are registered within the central trial database. Randomisation will be performed by using sequentially numbered medication packs available in each centre. Only the independent data manager has access to the computer-generated randomisation list in which the medication numbers are linked with atosiban or placebo. Treatment allocation is blinded to investigators, participants, clinicians and research coordinators. Randomisation will be balanced with varying block sizes of 2 and 4, and stratified by centre.

At study entry, baseline demographic, prior obstetric and medical history will be recorded into the web-based case report form accessible through a secure central website (Castor Electronic Data Capture, Ciwit B.V.).^21^ Details of delivery, maternal and neonatal assessments during pregnancy and postpartum period will be recorded on the same system. All data will be coded, processed and stored with adequate precautions to ensure patient confidentially. This is described in a separate data management plan.

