Maternal quality of life will be assessed at randomisation and at 3 months baby corrected age using the EuroQol (EQ-5D-5L) questionnaire. This consists of five dimensions (mobility, self-care, usual activities, pain/discomfort, anxiety/depression) that are rated using five levels (no problems, slight problems, moderate problems, severe problems, extreme problems).

Societal costs will be assessed using adapted versions of the iMTA Medical and Productivity Cost Questionnaires at 3 months corrected baby age. Cost data include costs of the intervention, other healthcare utilisation, patient and family costs and costs of productivity losses.

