### Statistical analysis

#### Data analysis

Data analysis will be performed according to the intention-to-treat principle. In the baseline table, categorical variables will be expressed as a number with the percentage of the total allocation arm. Continuous variables will be presented as mean with SD, as geometric mean with 95% CI or as median with IQR, whichever appropriate.

The main outcome ‘adverse neonatal outcome’ will be assessed on the infant level, using a log-binomial generalised estimating equations model to take into account the correlation of outcomes in multiples, resulting in an RR with accompanying 95% CI. To account for stratified randomisation by centre, we will also take centre into the model if the model converges.^29^ We will account for interdependence between outcomes in multiple pregnancies by considering the mother as a cluster variable.^30^

The other secondary outcome measures on the child level will be analysed similar to the primary outcome measure. Outcomes on the maternal level will be assessed by using a binomial regression model with log-link function. When a statistically significant difference in primary outcome is found between both groups, we will calculate the number needed to treat. Time to delivery will be evaluated by Kaplan-Meier estimates and Cox proportional hazard analysis, taking into account the different durations of gestation at study entry, and will be tested with the log rank test. A p value of <0.05 will be considered to indicate statistical significance.

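### The cost-effectiveness regressions adjust for confounders only if necessary, where a randomised trial stratified by centre calls for a fixed covariate set

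*Protocol article*

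**What the plan says.** The Cost-effectiveness analysis section of the protocol article sets the estimation rule: "Bivariate regression analyses will be used to estimate cost and effect differences between atosiban and placebo while adjusting for confounders if necessary". It names no covariate and does not say how, when or by whom necessity is judged. For uncertainty it says: "Bias-corrected and accelerated bootstrapping with 5000 replications will be used to estimate statistical uncertainty". It does not give the resampling unit.

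Four other places bear on this:

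- **Randomisation** (Procedures, recruitment, randomisation and collection of data): "Randomisation will be balanced with varying block sizes of 2 and 4, and stratified by centre".
- **Primary analysis** (Data analysis): centre enters the log-binomial model to reflect the stratified randomisation, provided the model converges. Multiples are handled by "considering the mother as a cluster variable".
- **Quality of life** (Outcome measures): "Maternal quality of life will be assessed at randomisation and at 3 months baby corrected age using the EuroQol (EQ-5D-5L) questionnaire".
- **Costs** (Outcome measures): "Societal costs will be assessed using adapted versions of the iMTA Medical and Productivity Cost Questionnaires at 3 months corrected baby age". They include patient and family costs and productivity losses.

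Cost-effectiveness is part of the stated Objective. The trial runs in three countries (Design and setting) and more than 40 hospitals (Strengths and limitations).

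**The concern.** Confounding in the usual sense does not arise between randomised arms. What remains is chance imbalance, which the standard error already allows for. The reasons to adjust are to respect the stratified design and to gain precision from prognostic baseline variables. Both are known in advance and do not depend on how the arms turn out.

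The phrase works the other way round. It permits an unadjusted model if someone judges that adjustment is not needed, and a model with chosen covariates if someone judges that it is. Two candidates are obvious:

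- Centre is the stratification factor and the article itself puts it in the primary model. Resource use and costs can plausibly differ between hospitals and countries.
- The EQ-5D value at randomisation is measured on the same woman with the same instrument as the later value.

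At stake are the width of the intervals for costs and effects, and hence the spread on the cost-effectiveness plane and the shape of the acceptability curve. A discretionary covariate set can also move the point estimates, and so leaves a choice between more and less favourable models.

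**Working it through.** **No figure to reproduce.** The cost-effectiveness section states no number that depends on adjustment; its only figure is the 5000 bootstrap replications. The article gives no between-centre variance, EQ-5D correlation or share of multiples. The inputs below are therefore assumptions, shown as ranges.

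**Step 1: what each section commits to.**

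| Item | Primary analysis | Cost-effectiveness analysis |
|---|---|---|
| Centre | Included, provided the model converges | Not named; adjustment only if judged necessary |
| Baseline EQ-5D | Not applicable | Collected, not named |
| Mother as cluster | Stated | Resampling unit not stated |

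The convergence proviso belongs to a log-binomial model. It is much less of an obstacle in regressions of costs and effects.

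**Step 2: leaving out centre.** With allocation balanced within centre, between-centre variation largely cancels from the treatment difference. A model without centre still counts it in the residual variance. The reported standard error is then too large by

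1/√(1 − ICC) − 1, where ICC is the between-centre share of variance.

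- ICC 0.05: 1/√0.95 − 1 = 2.6%
- ICC 0.10: 1/√0.90 − 1 = 5.4%
- ICC 0.20: 1/√0.80 − 1 = 11.8%

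A simulation with 40 assumed centres of 18 mothers, balanced within centre and analysed without centre, gave ratios of model-based to empirical standard error of 1.008 at ICC 0.05 and 1.022 at ICC 0.10. It used 2000 replications, so the Monte Carlo error is about 1/√(2 × 2000) = 1.6%. It supports the direction (slightly conservative) but is too coarse to fix the size.

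**Step 3: leaving out baseline EQ-5D.** Adjusting for a baseline value that correlates r with the outcome removes a share r² of the variance.

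- r = 0.2: r² = 4%; the unadjusted standard error is 1/√0.96 = 1.02 times the adjusted one
- r = 0.5: r² = 25%; the ratio is 1/√0.75 = 1.15

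EQ-5D is not a stratification factor, so here the unadjusted standard error is valid, only larger than it need be. The gain applies only if maternal utility is the effect. The section does not say which effect enters the incremental ratio and does not mention QALYs.

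**Step 4: direction.** Both omissions widen intervals. Neither makes them too narrow.

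**Step 5: the bootstrap, as a conditional only.** If individual infants were resampled, the design effect would be 1 + ρ·2t/(1 + t), with t the share of twin pregnancies and ρ the within-pair correlation.

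- t = 0.10, ρ = 0.3: 1 + 0.3 × 0.20/1.10 = 1.055; standard error understated by 1 − 1/√1.055 = about 3%
- t = 0.25, ρ = 0.7: 1 + 0.7 × 0.50/1.25 = 1.28; standard error understated by 1 − 1/√1.28 = about 12%

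If mothers are resampled, the understatement is nil.

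**The case against.** The strongest reply is that a journal article condenses. It names no covariates and so excludes none, and a list of covariates is normal content for an analysis plan or health-economic plan. The article announces a separate statistical analysis plan to be completed before data lock, which could fix the covariates before anyone sees results by arm. An unadjusted comparison of randomised arms is valid. The section on clinical outcomes does not govern the economic analysis, so the difference between the two is not a contradiction. Always entering more than 40 centres would be stricter than the primary analysis itself.

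Much of this stands. The missing covariate list is not the point, the timing of the judgement is not stated, and there is no formal contradiction. What it does not answer is that the conditional rule is stated, not merely left open: an analysis plan faithful to the article would inherit it. The worry about many centres is met by a random effect.

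A reader might also infer something stronger: that the bootstrap ignores clustering by mother, and that the uncertainty around costs and effects is therefore misstated. The article does not support this. It gives no resampling unit and nowhere says that infants are resampled. Women are randomised, EQ-5D is maternal and the costs include family costs, so the mother or family is a natural unit. The primary outcome is assessed on infants, so an infant-level effect in the ratio is possible, but the unit would still be unstated. Nor do omitted covariates produce false precision: by steps 2 and 3 they act in the opposite direction.

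**Conclusion.** The point holds as a minor improvement to a stated rule. Conditional adjustment for confounders suits a randomised comparison badly, leaves the covariates to judgement, and does not extend to the economic analysis the article's own decision to account for centre.

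The consequence is lost precision and room for discretionary modelling, not invalid inference. Under assumed values, the standard error is about 2.6% to 11.8% too wide if centre is left out (ICC 0.05 to 0.20), and a 4% to 25% variance reduction is forgone if baseline EQ-5D is left out (correlation 0.2 to 0.5, and only where maternal utility is the effect). The document fixes none of these inputs, so the actual size cannot be computed from it. The bootstrap unit is a matter for clarification only.

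**What to change.** Replace the conditional phrase with a fixed rule, in the protocol or the health-economic analysis plan, before data lock:

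- The cost and effect regressions both include the stratification factor, as a centre random effect or as country plus a centre random effect. With more than 40 hospitals and 760 women the average is at most 760/40 = 19 per centre, which favours a random effect over a separate parameter for each centre.
- Where maternal utility is the effect, that regression also includes the EQ-5D value at randomisation.
- No further covariates are added because of observed imbalance.

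As a clarification, state the bootstrap unit. If an infant-level effect enters the incremental ratio, resample mothers with all their infants, within arm.

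The cost is a change of wording and minor programming. Centre and baseline EQ-5D are already collected, and the only downside is a few extra model parameters.

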### Patient and public involvement

The preterm birth research line of the Dutch consortium is in close collaboration with two Dutch patient associations, the Vereniging van Ouders van Couveusekinderen (VOC, freely translated to society of parents of children admitted to NICU) and the Nederlandse Vereniging van Ouders van Meerlingen (freely translated to Dutch society of parents of multiples). They are involved in the design of new studies, updated on progress of running trials and informed of study results. Project members are invited speakers at yearly conferences of these societies to present on the progress of our preterm birth research line. At these conferences, surveys are being performed on patient preferences on study ideas. Tocolysis was deemed an important research issue. Both associations have written support letters to the funding agency ZonMw (The Netherlands organisation for health research and development) for the APOSTEL 8 study.

A project panel of parents who experienced a spontaneous preterm birth consisting of six couples was involved in the design of our study. A survey was performed during the design of the study among members of the closed Facebook group of the VOC, to address questions on whether they would be interested in participation in the APOSTEL 8 study.

The Dutch consortium has a website where it publishes all results of completed studies, and publishes the protocols of currently recruiting studies.

Presentations will be held at yearly conferences at patient organisations and updates on research are being published in the journal of the VOC.

### Ethics and dissemination

The Research Ethics Committee (REC) at the Amsterdam University Medical Centres, location AMC, approved this study. Additional regional approval was obtained for the remaining participating hospitals in The Netherlands. Furthermore, the study was approved by the REC of the National Maternity Hospital in Dublin, Ireland, and the REC of East Midlands—Derby in the UK. Protocol amendments will be communicated to a relevant parties. This trial is registered with the Nederlands Trial Register.

A manuscript with the results of the primary study will be published in a peer-reviewed journal. A separate manuscript will be written on the cost-effectiveness analysis. The results of this clinical trial will be presented at conferences and disseminated through publication in a peer-reviewed journal.
